**Methods:**

This study is a prospective, randomized, national multi-center trial. The trial comprises two strata: Stratum I compares cast-immobilization versus open reduction and internal fixation (ORIF) treatment of non-dislocated Lisfranc joint injuries. Stratum II compares PA versus ORIF in the treatment of dislocated injuries of the Lisfranc joint. The main hypothesis of stratum I is that the nonoperative treatment of non-dislocated Lisfranc injuries achieves a similar outcome compared with operative treatment (ORIF). The hypothesis of stratum II is that PA of dislocated Lisfranc injuries yields a similar functional outcome compared with ORIF, but that PA results in fewer secondary operations than ORIF. The main outcome measure is the American Orthopaedic Foot and Ankle Society (AOFAS) Midfoot score and the secondary outcome measures are Visual-Analogue-Scale Foot and Ankle (VAS-FA), Visual-Analogue-Scale (VAS), rate of secondary operations and other treatment-related complications. The results will be analyzed after the 2-year follow-up period.

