## Methods/design

The study is a prospective, randomized, national multicenter trial. The trial centers are Tampere University Hospital and Seinäjoki Central Hospital. The trial has been designed to compare the nonoperative and operative treatment of Lisfranc injuries. The trial includes two strata: Stratum I compares nonoperative treatment and operative treatment with ORIF for non-dislocated Lisfranc injuries. Stratum II compares ORIF and PA in dislocated Lisfranc injuries.

The primary outcome in this study is the AOFAS [54] measured after 6, 12 and 24 months. The secondary measured outcomes after 6, 12 and 24 months are VAS [55], VAS-FA [52], number of secondary operations (implant removal, secondary arthrodesis) and number of other treatment-related complications.

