### Hypotheses

Our primary hypotheses in the study are the following:i)The hypothesis of stratum I is that nonoperative treatment of non-dislocated Lisfranc injuries yields better outcome in terms of AOFAS, VAS and VAS-FA score compared with operative treatment (ORIF).ii)The hypothesis of stratum II is that PA of dislocated Lisfranc injuries yields better functional outcome in terms of AOFAS, VAS and VAS-FA score compared with ORIF, and PA results in fewer secondary operations than ORIF.

The results of both strata will be analyzed and reported separately.

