### Power analysis

In this trial, the widely recognized AOFAS will be used as the main outcome measure. The clinically significant difference in AOFAS has been reported to be 8.36 (SD 11.16) points [56]. Assuming a 10-point difference in the AOFAS score and a standard deviation of 12 points, the estimated sample size is 23 patients (delta = 10, sd = 12, alpha = 0.05, power 0.8). We will assume a 20% drop-out rate in both groups, and therefore the total patient count needed for both stratums will be 56 patients. Due to block randomization in blocks of ten, 60 patients will be recruited.

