### Statistical analysis

The baseline characteristics will be reported as mean (standard deviation), median (quartiles) or proportion. Study groups will be compared using t-test, Mann-Whitney U or Fisher’s exact test. Primary (AOFAS) and secondary outcomes (VAS-FA, VAS, complications, secondary surgery) will be compared at 12 months and 24 months using the Mann-Whitney U test. The results will be presented with 95% confidence intervals, and therefore a *p*-value of < 0.05 will be considered statistically significant. The data will be analyzed according to the intention-to-treat principle, assuming the patients change group during the study. The statistical analysis will be performed with SPSS© version 22.

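### Complications and secondary surgery are event outcomes, but the plan fixes a Mann-Whitney U test for them: no risk difference stands behind the promised confidence interval, and the form of the p-value is left open.

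*Protocol article*

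**What the plan says.** The Statistical analysis section assigns one test to the primary outcome and every secondary outcome: "secondary outcomes (VAS-FA, VAS, complications, secondary surgery) will be compared at 12 months and 24 months using the Mann-Whitney U test". The sentence before it, which follows the description of baseline summaries, reads "Study groups will be compared using t-test, Mann-Whitney U or Fisher’s exact test"; it ties no test to any outcome. The section then states that "The results will be presented with 95% confidence intervals", without naming an effect measure.

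Methods/design describes the event outcomes as "number of secondary operations (implant removal, secondary arthrodesis) and number of other treatment-related complications", while the Abstract (Methods) speaks of "rate of secondary operations and other treatment-related complications". Under Hypotheses, the stratum II primary hypothesis includes that "PA results in fewer secondary operations than ORIF".

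The Power analysis section covers AOFAS only: "the estimated sample size is 23 patients (delta = 10, sd = 12, alpha = 0.05, power 0.8", followed by "We will assume a 20% drop-out rate in both groups", a need of 56 and a target of 60. It gives no figure for complications or secondary surgery.

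**The concern.** A rank test suits AOFAS, VAS-FA and VAS. Complications and secondary operations are different: per patient they are mostly 0 or 1, occasionally 2, so most observations are tied. This has two consequences.

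- **Effect size.** The quantity of interest is how many fewer patients need another operation. The rank test does not report that, so for this outcome the promised interval has no stated quantity behind it.
- **P-value.** With heavy ties and small arms, the asymptotic and exact forms of the test can differ by a factor of two or more, and the protocol does not say which it will use.

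At stake is one limb of the stratum II primary hypothesis. By the article's own review of earlier trials, secondary surgery is where the two operations differ most clearly.

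**Working it through.** **1. The plan's own figure and the arm sizes.** Inputs from Power analysis: difference 10, SD 12, alpha 0.05 (taken as two-sided), power 0.80.

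n per arm = 2 × (1.960 + 0.842)² × 12² / 10² = 2 × 7.85 × 1.44 = 22.6, so 23. This reproduces the stated 23. With 20% added: 23 × 1.2 = 27.6, so 28 per arm, and 2 × 28 = 56 for one two-arm comparison. The text, however, describes 56 as the total for both strata. Two readings of the 60 therefore remain open:

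- 60 over both strata: 60 / 4 = 15 per arm, and 15 × 0.8 = 12 after dropout.
- 60 per stratum: 60 / 2 = 30 per arm, and 30 × 0.8 = 24 after dropout.

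All four sizes are used below.

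**2. What the test is on yes/no data.** The tie-corrected asymptotic Mann-Whitney statistic, without continuity correction, equals Pearson's chi-square × (N − 1)/N. The exact permutation version equals Fisher's exact test.

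Example, 7/12 against 2/12:
- Pooled proportion 9/24 = 0.375; difference 5/12 = 0.4167.
- Chi-square = 0.4167² / (0.375 × 0.625 × 2/12) = 0.1736 / 0.03906 = 4.444.
- × 23/24 = 4.259, so p = 0.039. Fisher's p = 0.089.

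Example, 4/12 against 0/12:
- Chi-square = 0.3333² / (0.1667 × 0.8333 × 2/12) = 4.80; × 23/24 = 4.60, so p = 0.032.
- Fisher's p = 2 × C(12,4)/C(24,4) = 2 × 495/10,626 = 0.093.

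**3. What effect estimate it supplies.** Take 7/12 against 2/12 again. Of the 144 between-arm pairs, 7 × 10 = 70 differ by +1, 5 × 2 = 10 by −1, and 64 by 0. The median pairwise difference (Hodges-Lehmann shift) is 0, because 10 + 64 = 74 of 144 are at or below 0. Yet the risk difference is 41.7 percentage points, Newcombe 95% interval 3.1 to 67.0. The usual companion estimate of the rank test thus shows no effect where the data show a large one.

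**4. Size, power and disagreement.** All 2×2 tables were enumerated at each arm size, with exact binomial probabilities. MW is the asymptotic tie-corrected form. Illustrative rates come from the ligamentous-injury randomized trial described under Previous studies: conversion or revision arthrodesis 7/20 (ORIF) and 1/21 (PA); implant removal 16/20 and 4/21.

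| Per arm | 12 | 15 | 24 | 30 |
|---|---|---|---|---|
| Maximum type I error, MW | 6.4% | 4.3% | 6.0% | 5.5% |
| Maximum type I error, Fisher | 2.3% | 1.8% | 2.9% | 2.7% |
| Tables on opposite sides of 0.05 | 16 of 169 | 20 of 256 | 36 of 625 | 54 of 961 |
| Probability of this, 7/20 v 1/21 | 18.0% | 16.5% | 9.9% | 9.0% |
| Probability of this, 16/20 v 4/21 | 9.3% | 6.1% | 0.4% | 0.1% |
| Power at 7/20 v 1/21, MW | 44% | 57% | 82% | 89% |
| Power at 7/20 v 1/21, Fisher | 26% | 41% | 72% | 80% |

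**5. Which test is the outlier.** Boschloo's unconditional exact test was run on borderline tables.

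| Table | MW | Boschloo | Fisher |
|---|---|---|---|
| 7/12 v 2/12 | 0.039 | 0.042 | 0.089 |
| 4/12 v 0/12 | 0.032 | 0.045 | 0.093 |
| 6/12 v 1/12 | 0.028 | 0.029 | 0.069 |
| 8/15 v 2/15 | 0.022 | 0.023 | 0.0502 |
| 6/15 v 1/15 | 0.034 | 0.043 | 0.080 |

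Over all tables, MW and Boschloo disagree at 0.05 in 4 of 169 (12 per arm) and 0 of 256 (15 per arm). The gap to Fisher is therefore mainly Fisher's conservatism.

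**The case against.** Several points on the other side are sound.

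- **The test is not invalid.** A reader might infer from the p-value pairs that Mann-Whitney is unreliable at these sizes. The enumeration does not support that: its type I error never exceeds 6.4%, and at 15 per arm it stays below 5%. An exact unconditional test mostly agrees with it at 12 and 15 per arm.
- **Arms of 12 to 15 are not established.** The Power analysis wording permits them, but its arithmetic fits one two-arm comparison, which points to 24 to 30. At the larger sizes and the cited implant-removal rates, the two forms almost never disagree.
- **The outcomes are worded as numbers.** A rank test on per-patient counts is legitimate, and at least one event is a coarser endpoint.
- **The interval need not come from the test.** A risk difference could be reported beside any p-value, and a separate analysis plan may name it. It would be wrong to conclude that no effect size can be reported. On yes/no data the rank test's superiority probability is even 0.5 plus half the risk difference (0.5 + 0.417/2 = 0.708 in the example), although the plan does not name it.
- **Fisher's test is mentioned,** in a sentence not expressly confined to baseline.

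What survives is narrower. The sentence that names these outcomes assigns Mann-Whitney to them, and it is more specific than the general list of tests before it. Followed as written, it leaves the form of the p-value open and attaches no interpretable effect measure to part of a primary hypothesis.

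**Conclusion.** The point holds as an analysis choice that should be improved; it is not an error that invalidates the trial. The main weakness is the effect measure: for complications and secondary surgery the named test does not supply a risk difference or ratio for the promised interval. That is true at any arm size. The second weakness is the open choice between asymptotic and exact p-values. For 7/20 against 1/21 it changes the conclusion with probability 9.0% to 18.0%; for 16/20 against 4/21, with probability 0.1% to 9.3%.

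These figures assume yes/no data per patient, a two-sided 0.05 level, the asymptotic test with tie correction and no continuity correction, and true rates equal to those of one small cited trial. The ranges cover both readings of the sample size. The primary AOFAS comparison is not affected.

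**What to change.** Replace the single-test sentence for the two event outcomes with text along these lines: at 12 and at 24 months, within each stratum, the proportion of patients with at least one secondary operation, and separately with at least one treatment-related complication, will be compared by a two-sided Boschloo exact test; the risk difference will be given with a Newcombe 95% confidence interval; the number of events per patient will be tabulated by arm. Keep rank tests for AOFAS, VAS-FA and VAS.

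The change needs no new data or patients. Its costs:

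- Reducing counts to at least one event drops repeat events from the test, which is why the counts are reported alongside.
- If Fisher's test is preferred because the plan already mentions it, power falls at the rarer event rates (7/20 against 1/21): 26% rather than 44% at 12 per arm, and 80% rather than 89% at 30. At 16/20 against 4/21 Fisher still has 83% power at 12 per arm.
- A test-based p-value and a Newcombe interval can disagree at the margin. With 4/12 against 0/12, Fisher gives 0.093 while the interval is 2.2 to 60.9 points. The plan should say which one decides.
- The team should confirm that its software offers the chosen test.

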### Study material

All information will be sent to Tampere University Hospital and the gathered material will be stored in a study registry. The registry is protected with passwords given only to the authors and the secretary of the study group and the data will be deleted 15 years after the end of the study.

### Ethics

The study protocol and additional papers, including consent form, patient information form and questionnaires have been approved by the Regional Ethics Committee of Tampere University Hospital**.** (Approval number R11152, 11th November 2011). All participants will provide a written consent to participate.

### Time schedule

The recruitment of patients started in 2011 and it will be continued until the number of patients achieves the estimated volume of power analysis. The final results will be analyzed after the 2-year follow-up period of the last recruited patient. In October 2017, 51 patients had been included in the study. The final report will be published by the end of 2021.

## Discussion

This publication presents a prospective, randomized, national multi-center trial. It gives details of patient flow, randomization, aftercare and methods of analysis of the material and ways to present and publish the results. The limitations of this study are limited patient blinding due to the nature of the treatment (operative versus nonoperative) and using a primary outcome measure (AOFAS) that has not been validated in Finnish. The strength of this study is that this is the first study to compare the nonoperative and operative treatment of Lisfranc joint injuries in a prospective and randomized study setting with an adequate number of patients. As the previous literature provides only two contradictory randomized controlled trials on this matter, the benefits of this study are to provide evidence-based knowledge on the treatment of these injuries.

## Abbreviations

ADL: Activities of daily living
AOFAS: American Orthopaedic Foot and Ankle Society
CT: Computed tomography
ER: Emergency room
K-Wire: Kirschner-Wire
MFA: Long-Form Musculoskeletal Function Assessment
MT: Metatarsal
ORIF: Open reduction and internal fixation
PA: Primary arthrodesis
PFS: Baltimore Painful Foot Score
SF-36: Short-Form 36
SMFA: Short-Form Musculoskeletal Function Assessment
TMT: Tarsometatarsal
VAS FA: Foot and Ankle Visual-Analogue-Scale
VAS: Visual-Analogue-Scale
